## Abstract

**Background:**

The American Heart Association Position Statement on Cardiovascular Health Promotion in Public Schools encourages school-based interventions for the primary prevention of cardiovascular disease (CVD) through risk factor prevention or reduction in children with an emphasis on creating an environment that promotes healthy food choices and physical activity (PA). In an effort to address issues related to CVD risk factors including obesity in Michigan children, a multi-disciplinary team of Michigan State University (MSU) faculty, clinicians, and health profession students was formed to "(S)partner" with elementary school physical education (PE) teachers and MSU Extension staff to develop and implement a cost-effective, sustainable program aimed at CVD risk factor prevention and management for 5^th ^grade students. This (S)partnership is intended to augment and improve the existing 5^th ^grade PE, health and nutrition curriculum by achieving the following aims: 1) improve the students' knowledge, attitudes and confidence about nutrition, PA and heart health; 2) increase the number of students achieving national recommendations for PA and nutrition; and 3) increase the number of students with a desirable CVD risk factor status based on national pediatric guidelines. Secondary aims include promoting school staff and parental support for heart health to help children achieve their goals and to provide experiential learning and service for MSU health profession students for academic credit.

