#### Primary aims

1. To increase the percentage of students achieving national recommendations for physical activity and nutrition behaviors;

2. To improve the public school students' knowledge, attitudes and self-efficacy about heart healthy nutrition and physical activity behaviors as recommended by national guidelines;

3. To improve or maintain the number of students with a desirable CVD risk factor status;

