#### Statistical Power Calculations

A power calculation indicated that based on an N of 180 and 90 children in each group (SPartners for Heart Health versus comparison group), the following changes will need to be achieved for the primary aims of this study. With respect to the percentage of students achieving the national recommendation for physical activity; based on an estimate of 50% of the students achieving physical activity guidelines at baseline, it will be possible to detect a difference of 18% in the percentage achieving the guidelines (an increase from 50% to 59%) with an alpha level of 0.05 and a power of 80% using a one-tailed test. For nutrition behavior we chose total dietary fiber intake since it is surrogate marker of fruit, vegetable, whole grain and legume intake. Based on an estimated baseline mean intake of 12 ± 8.8 grams of dietary fiber per day, it will be possible to detect a difference of 3.3 grams of fiber per day with an alpha level of 0.05 and 80% power using a one-tailed test.

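### The power statement rests on an unexplained one-tailed 0.05 test for each of two aim 1 endpoints, and aim 3 is worded in two different ways

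*Protocol article*

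**What the plan says.** The Statistical Power Calculations section works "based on an N of 180 and 90 children in each group" and introduces its results by saying that "the following changes will need to be achieved for the primary aims of this study". It then gives two endpoints.

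- **Physical activity:** "based on an estimate of 50% of the students achieving physical activity guidelines at baseline", the study is said to be able to "detect a difference of 18% in the percentage achieving the guidelines (an increase from 50% to 59" per cent), "with an alpha level of 0.05 and a power of 80% using a one-tailed test".
- **Dietary fibre:** from a baseline mean of 12 g per day with a standard deviation of 8.8 g, a difference of 3.3 g per day is detectable "with an alpha level of 0.05 and 80% power using a one-tailed test".

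Both endpoints fall under the first of the three primary aims, which concerns activity and nutrition behaviours. For aims 2 and 3 the article states no test, alpha level, sidedness or power.

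Aim 3 appears in two forms. The abstract gives it as "increase the number of students with a desirable CVD risk factor status based on national pediatric guidelines". The Primary aims section gives it as "To improve or maintain the number of students with a desirable CVD risk factor status".

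In the Discussion the article says that schools were not randomised, that blinding is impossible, and that other health initiatives may start in a community during the study.

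**The concern.** A one-tailed test is defensible when a difference in the other direction is impossible or would not matter. Neither is argued here, and the article's own description of the design points the other way. With two schools per arm and no randomisation, baseline differences, local initiatives or secular change could favour the comparison schools. A test directed at benefit cannot declare that result for activity or fibre. The Discussion makes wider adoption depend on the model being found effective, so the direction of evidence matters.

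Two further points follow.

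- The two endpoints each take a full 0.05, and nothing ranks them. The order of the aims gives no help: the abstract puts knowledge and attitudes first and behaviours second, and the Primary aims section reverses this.
- Under the *increase* wording, aim 3 is a claim of improvement. Under the *improve or maintain* wording, unchanged numbers could be presented as meeting a primary aim.

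**Working it through.** **Inputs.** From Statistical Power Calculations: n = 90 per group, alpha 0.05, activity 50% against 68% (reading the stated 18% as percentage points), fibre difference 3.3 g, SD 8.8 g. Normal quantiles: 1.645 (one-sided 0.05), 1.960 (two-sided 0.05), 0.842 (80% power). Children are treated as independent throughout, so clustering in four schools is not included.

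**Step 1: reproduce the stated figures (one-sided).**

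*Fibre.* SE = 8.8 × √(2/90) = 1.312 g.
- Power = Φ(3.3/1.312 − 1.645) = Φ(0.871) = 80.8%.
- Detectable difference = (1.645 + 0.842) × 1.312 = 3.26 g.

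*Activity.* Mean proportion 0.59.
- SE under the null = √(2 × 0.59 × 0.41/90) = 0.0733.
- SE under the alternative = √((0.50 × 0.50 + 0.68 × 0.32)/90) = 0.0721.
- Power = Φ((0.18 − 1.645 × 0.0733)/0.0721) = Φ(0.824) = 79.5%.
- Detectable difference: about 18.1 points.

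Both agree with the article.

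**Step 2: the same inputs at two-sided 0.05.**

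*Fibre.*
- Power = Φ(2.516 − 1.960) = Φ(0.556) = 71.1%.
- Detectable difference = (1.960 + 0.842) × 1.312 = 3.68 g.

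*Activity.*
- Power = Φ((0.18 − 1.960 × 0.0733)/0.0721) = Φ(0.504) = 69.3%.
- Detectable difference: about 20.3 points.

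| Endpoint | Power, one-sided | Power, two-sided | Detectable, one-sided | Detectable, two-sided | n per group for 80%, two-sided |
|---|---|---|---|---|---|
| Activity, 50% v 68% | 79.5% | 69.3% | 18.1 points | 20.3 points | 117 |
| Fibre, 3.3 g | 80.8% | 71.1% | 3.26 g | 3.68 g | 112 |

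The two-sided calculation does not give the stated 80%, so the one-tailed setting was really used and is not a slip of wording. The detectable differences grow by 20.3/18.1 = 1.12 and 3.68/3.26 = 1.13, about 12%.

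**Step 3: family-wise error, if either endpoint alone counted as success.** With two independent one-sided 0.05 tests, 1 − 0.95² = 9.75%. With an assumed correlation between the test statistics, a bivariate normal calculation gives 9.3% at 0.3, 8.8% at 0.5 and 7.5% at 0.8. Each single test keeps its own 5% error; only the joint rate exceeds it.

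**Step 4: the activity sentence.** An increase from 50% to 59% is 9 points, which is 18% only in relative terms (9/50). At 90 per group, 50% against 59% has 33.2% power one-sided and 22.6% two-sided. Only the 18-point reading agrees with 80% power, so the two figures must be reconciled before the activity result is restated.

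**Step 5: the two wordings of aim 3.** The abstract asks for more students with desirable status. The Primary aims section asks for more or the same number. The first is not met by no change; the second, read literally as a within-group count, is.

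**The case against.** The aims are directional, the one-tailed choice is disclosed, and the abstract calls this a pilot effectiveness study. The Discussion is open about the lack of randomisation and the few schools. A two-sided test would not remove bias from non-randomised assignment. All of this is fair. It makes the choice less serious, but it does not explain why a result favouring the comparison schools should be undeclarable.

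The article is also a condensed account. A rule for multiple endpoints or for success may stand in a full protocol or analysis plan that is not shown. That objection stands, and it is why the family-wise figure is only conditional. It does not reach the published power figures, which are tied to the one-tailed setting, or the two wordings of aim 3.

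Three stronger readings are tempting, and the article does not support them.

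- A reader might infer that all three primary aims are to be tested one-tailed at 0.05. The article states this for two aim 1 endpoints only.
- A reader might count every measured outcome as a separate primary test and arrive at a family-wise error above one half. The article specifies no such set of tests, many of the measures would be correlated, and aim 3 is worded as a single quantity.
- A reader might conclude that a superiority test can never support maintenance. It can: if risk status worsens in comparison schools and holds steady in intervention schools, that is a between-group benefit which such a test can detect. Nor does any stated rule let a null between-group result count as success; the wording merely leaves room for it.

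**Conclusion.** The concern holds in a limited form. The article bases its power statement on an unexplained one-tailed 0.05 for activity and for fibre, in a non-randomised comparison where worsening is plausible and could not be declared on those endpoints. At the conventional two-sided 0.05, the claimed 80% falls to about 69% and 71%. These figures assume 90 independent children per group and the 18-point reading; clustering would make them less favourable.

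The joint false-positive rate of 7.5% to 9.75% applies only if success on either endpoint is enough and no rule elsewhere prevents it. The inconsistency in aim 3 is plain on the page and depends on no assumption.

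**What to change.** 1. State two-sided 0.05 for both endpoints. Restate the detectable differences at 90 per group as about 20 percentage points and 3.7 g per day, and say that they are before any allowance for clustering.
2. In the same edit, reconcile the 18% with the 50% to 59% in the activity sentence.
3. Test activity first, and fibre only if activity is significant.
4. Word aim 3 identically in the abstract and the Primary aims section, as the difference between intervention and comparison schools in the proportion with desirable risk factor status, so that a null result cannot be read as success.

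**Cost.** If the restated differences are accepted, this is a change of wording, with no added children or measurements; the detectable differences grow by about 12%. Keeping 80% power at 18 points and 3.3 g would instead need 117 and 112 per group, or 234 and 224 in total, against the 180–200 anticipated. The fixed order also means that fibre cannot be claimed if activity fails. With 80% power for each at the restated differences, and assuming independence, both would succeed with probability 0.8 × 0.8 = 64%.

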## Discussion

Following the completion of the effectiveness study described here, we intend to conduct a large-scale effectiveness trial with an adequate number of schools necessary for conducting school level statistical analysis (e.g., linear mixed models). We will develop partnerships with other colleges and universities which will be instrumental in the long-term goal of disseminating the (S)partner for Heart Health intervention in other regions of Michigan. In addition to partnering with other colleges and universities in Michigan, we plan to expand our relationship with MSU Extension through the agencies located in all counties in Michigan. In addition to the investigative team, the extension staff will be involved in supporting the training of the college students and assisting public school teachers in implementing the interventions. For example, Central Michigan University (CMU) could have a program based on their mascot called "Chippewas for Heart Health." In collaboration with the MSU investigative team, CMU faculty, staff, students, and MSU Extension staff would implement a program in counties surrounding Mount Pleasant, Michigan. This model (if determined to be effective) could feasibly be sustained long-term with modest financial support due to several reasons. The measurement and intervention battery (including the web-based tracking) could be adopted by any college and university that has allied health profession students and/or medical or nursing students. The fact that the key personnel conducting the measurement and the intervention consists of students receiving academic credit for this experience creates an ongoing flow of personnel and limits the costs associated with employing a research staff. Additionally, a partnership with MSU Extension will also help this program model be sustainable. Lastly, the measurement battery of tests could be reduced and the focus would be on monitoring behavior change.

Despite the many strengths of the intervention, there are some potential limitations. To date, we have only conducted a small pilot and feasibility study to prepare for the upcoming effectiveness study. Although formative assessment and the pilot have been performed, the goal of the upcoming investigation is to gain further information that will assist with a larger-scale implementation of the intervention. Thus, given the small number of schools that will be involved in the effectiveness study, it will not be possible to perform school-level analyses. In addition, schools were not randomized and blinding is impossible. Furthermore, over a 9-month period it will be a challenge to observe significant between group changes when comparing the (S)partner intervention with control schools. Other potential limitations that are difficult to anticipate but will be documented are concurrent health initiatives that may begin in a community during the effectiveness study. Finally, the number of (S)partners and medical students available and willing to be involved with this project during any given semester could be limiting to the number of schools and public school students that are served.

In summary, we have described the background and rationale, study design, measurement procedures, intervention components, and process evaluation procedures for (S)Partners for Heart Health. We anticipate this intervention will lead to an effective heart healthy education and behavior change model that can be cost effectively adopted into public schools to promote a desirable CVD risk factor status in school children. This will be achieved in part by using existing resources (MSU Extension) and activating college students (medical students and allied health professional students) in service learning through independent- and elective- academic credit, that offer training and experiential learning that cannot be achieved in the classroom setting. Although we are currently implementing this program in 5^th ^grade classrooms, the same methods can be applied to other grades with minor modifications (e.g., selection of different curricula). Ultimately, this program aims to reduce premature morbidity (obesity, hyperlipidemia, hypertension, diabetes, etc.) and mortality and their associated health costs by sustaining or improving heart healthy behaviors that influence CVD risk factor status in 5^th ^grades students acutely and long-term.

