**Methods/Design:**

This pilot effectiveness study was approved by the MSU IRB. At the beginning and the end of the school year students undergo a CVD risk factor assessment conducted by MSU medical students and graduate students. Key intervention components include eight lesson plans (conducted bi-monthly) designed to promote heart healthy nutrition and PA behaviors conducted by PE teachers with assistance from MSU undergraduate dietetic and kinesiology students (Spartners). The final 10 minutes of each lesson, MSU Spartners conduct small breakout/discussion groups with the 5^th ^grade students. Additionally, each Spartner case manages/mentors two to three 5^th ^grade students using a web-based goal setting and tracking protocol throughout the school year.

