#### Secondary aims

1. To promote school staff and parental support for heart healthy activities to help children achieve their heart health goals;

2. To provide applied hands-on learning and training for MSU health profession students.

There are several unique aspects of the (S)partners for Heart Health program that are designed to address the limitations of previous school-based cardiovascular health trials. The project is designed to be cost-effective and sustainable by utilizing undergraduate dietetic and kinesiology students and second year medical students to play key roles in the program intervention and measurement assessment, respectively. The kinesiology and dietetics students will (S)partner with 5^th ^grade students by mentoring and case managing the students using a secure (password protected) web-based goal setting and tracking protocol and through involvement in monthly lesson plans and small breakout meetings. The medical students will carry out the measurement protocol.

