#### Web- based goal tracking and education

In the time between monthly visits to the public schools for lesson plans and small group meetings, (S)partners will communicate with the school children via a secure website  which is monitored by study coordinators graduate students and faculty. This web-based platform allows for the facilitation of behavioral goal setting for nutrition and physical activity using a behavioral tracking tool, as well as links to educational modules to promote the achievement of heart healthy behavioral and educational goals and reinforce classroom educational efforts. Our protocol is developed based on previous relevant research involving goal setting [35,36,47-50] and knowledge gained from the pilot study. Students are required to log on weekly at school and set their activity and nutrition goals for the week, which will be measurable and based on national guidelines for nutrition and physical activity [51-54]. Students will maintain the same goal for a minimum of three weeks or until they achieve it. For example, a student who reports a low intake of whole grains (1 serving per day) may set a goal to have 3 or more servings of whole grains per day. Success will be based on achieving the goal at least 5 of 7 days per week. The students will log their progress for their nutrition and physical activity goals on tracking cards and then they will log their progress weekly on the (S)partner website. The (S)partners will give guidance to help them achieve the goal. To avoid barriers to computer access, there will be a set time weekly at the school during which the 5^th ^grade students report on their goals and communicate with their (S)partner. If children have access at home, they will be encouraged to access the website more often.

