#### Measurement protocol

Assessments will be conducted during September (pre-intervention) and May (post-intervention) by MSU medical students and staff. This service is part of the medical students' community outreach elective and is an ongoing elective that will promote cost-effective, long-term sustainability of the study protocol. The assessment includes physical activity and nutrition behaviors; lifestyle and heart health knowledge, attitudes and behaviors for nutrition and physical activity; and self-efficacy toward nutrition and exercise behavioral goals. The CVD risk appraisal includes resting blood pressure, blood cholesterol, C-reactive protein, body size and composition, and aerobic fitness. The baseline assessment data will help guide the heart healthy nutrition and exercise goal setting mentioned in the previous section.

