#### Cardiovascular disease risk factors

As previously indicated, the CVD risk factor profile will include: body mass index (BMI), body fat, waist circumference, resting blood pressure, blood cholesterol, C-reactive protein, and aerobic fitness. Obesity indicators will include measurements of body size and composition. The BMI will be calculated from measured stature and body mass according to standardized procedures. Waist circumference will be measured using a Gullick Anthropometric Tape at the level of the umbilicus. For anthropometric indices, the medical students will be trained prior to data collection by the investigators, and intra- and inter-observer measurement error will be determined. This type of training protocol has resulted in small measurement errors during the actual measurement period (SEM = 0.3 cm standing height; 0.1 kg body mass; 0.2 cm WC). Body fatness will be estimated using a foot-to-foot bioelectric impedance device (Tanita Corporation, Tokyo, Japan). Resting blood pressure will assessed using manual blood pressure device with the appropriate sized cuff on the subject's upper right arm following standardized procedures recommended by the Joint National Committee (USA) on Prevention, Diagnosis and Management of Hypertension [65]. Blood samples will be obtained by fingerprick and collected in heparinized capillary tubes. Blood sampling by fingerprick has been chosen for reasons of compliance and feasibility. Compared to venipuncture, blood sampling by fingerprick is less invasive and is less likely to deter subjects from participating; fingerprick is also more feasible for a field-based setting. One sample will be analyzed for total cholesterol, high-density lipoprotein-cholesterol, and triglycerides within 5 minutes by a portable cholesterol/glucose analyzer according to the protocol of the manufacturer (Cholestech LDX System, Hayward, CA). A second sample will be analyzed for C-reactive protein also using the Cholestech LDX. Cardiorespiratory fitness will be estimated using the PACER test which consists of an endurance-type shuttle run which will be conducted by program staff trained to conduct this procedure following standardized procedures [66].

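### The statement that blinding is impossible is too broad: at least partial masking of outcome assessors is feasible for the observer-dependent part of primary aim 3

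*Protocol article*

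**What the plan says.** The Discussion lists among the study's limitations that "schools were not randomized and blinding is impossible". It does not separate pupils, teachers, mentors and assessors, and gives no reason specific to assessors.

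Elsewhere the article divides the work:

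- **Delivery.** Physical education teachers teach the lessons with help from the undergraduate mentors (Lesson plans). On mentoring, Secondary aims says: "The kinesiology and dietetics students will (S)partner with 5^th ^grade students by mentoring and case managing the students".
- **Measurement.** Secondary aims says: "The medical students will carry out the measurement protocol". The Measurement protocol section widens this: "Assessments will be conducted during September (pre-intervention) and May (post-intervention) by MSU medical students and staff". The Abstract describes the assessment as "conducted by MSU medical students and graduate students". The Cardiovascular disease risk factors section gives the PACER test to trained program staff.
- **Oversight of delivery.** The website through which mentors reach the children is "monitored by study coordinators graduate students and faculty" (Web-based goal tracking and education).

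On method, the Cardiovascular disease risk factors section says "Resting blood pressure will assessed using manual blood pressure device". Waist is taken by tape and fitness by shuttle run. Lipids, C-reactive protein and body fat are read from instruments.

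**The concern.** An unqualified claim that blinding is impossible closes off a safeguard that the article's own staffing makes available. Primary aim 3 concerns the number of students with a desirable cardiovascular risk factor status, and three of its inputs involve an observer's judgement: the reading of a manual cuff, the placing and tension of a tape, and the conduct and scoring of a shuttle run.

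An assessor who knows the school's group and expects the programme to work may, without intending to, record slightly better values in the (S)partners schools. With four non-randomised schools and no school-level analysis, nothing in the design would separate such a tendency from a programme effect. The stated protections are training, standardised procedures and, for anthropometry, determination of intra- and inter-observer error. They limit inconsistency and observer discretion. They do not address knowledge of group.

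**Working it through.** The article gives no figure for assessor bias, so the main check compares its sections.

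**1. Who could be masked?**

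| Group | Stated role | Can allocation be withheld? |
|---|---|---|
| Pupils, PE teachers, mentors | Receive or deliver the programme | No |
| Medical students | Measurement; no delivery role stated | At least partly |
| Staff, program staff | Share measurement; run PACER | Depends on their other duties, which are not stated |
| Graduate students | Assessors in the Abstract; website monitors in the web section | Not if the same individuals do both |

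The blanket statement therefore fails for at least one group, and that group does much of the measuring.

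**2. How complete could masking be?**

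- *September.* Lessons start after baseline measurement, so cues should be few. But teachers are trained before the school year, the bulletin board is planned to run throughout the year (School Support), and no start date after baseline is given for the board, the principal's announcements or the newsletters. Medical students are also taught the project aims and the research protocol (Medical student recruitment and preparation; Table 1).
- *May.* Whole schools have had the programme for most of a school year. Displays and children's remarks will reveal the group to some assessors.

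Masking would be partial on both occasions, and weaker in May.

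**3. Which outcomes would gain?**

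- Gain: manual blood pressure, waist circumference, PACER.
- Little gain: lipids, C-reactive protein and impedance (instrument-read); pedometer steps (recorded by the child); fiber (food frequency questionnaire). Steps and fiber underlie the two outcomes in Statistical Power Calculations.

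**4. How sensitive could a comparison be? (illustration only)**

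From the article: 90 children per group and one-tailed alpha 0.05 (Statistical Power Calculations, where they are stated for physical activity and fiber only). Assumed, because the article gives neither: systolic SD of 9 to 11 mmHg and observer bias of 1 to 2 mmHg. Also assumed: independent children, no true effect, and a comparison of mean systolic pressure.

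SE = SD × √(2/90) = SD × 0.1491

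False-positive rate = 1 − Φ(1.645 − bias/SE)

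| SD (mmHg) | SE | Bias 1 mmHg | Bias 2 mmHg |
|---|---|---|---|
| 9 | 1.342 | 1 − Φ(0.900) = 0.184 | 1 − Φ(0.154) = 0.439 |
| 11 | 1.640 | 1 − Φ(1.035) = 0.150 | 1 − Φ(0.425) = 0.335 |

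The same formula for any continuous measure, with bias in SD units and SE = 0.1491, gives 0.165 for a bias of 0.1 SD, 0.381 for 0.2 SD and 0.643 for 0.3 SD.

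**The case against.** The strongest reply has five parts.

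1. **The measurers are not cleanly separate.** Staff and graduate students also assess, and program staff run PACER. This stands. Not telling the medical students the allocation would not by itself mask the shuttle run, so the remedy has to cover everyone at the three stations.

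2. **September masking cannot be assumed complete.** A reader might infer that it can, because lessons have not begun. The documents do not support that: teachers are already trained, some school-wide components have no stated start after baseline, and assessors are taught the protocol. A flat promise that assessors will be blinded would replace one overstatement with another.

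3. **The graduate-student overlap is only possible.** A reader might infer that the same people monitor the website and measure the children. The two sections name the same category of person, not the same individuals. What stands is that nothing in the article rules the overlap out.

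4. **The reach is narrow and the figures are assumed.** The two powered outcomes would gain little, and no one-tailed blood pressure test is specified. Both points stand. They limit the weight of the finding without removing it, because aim 3 is a primary aim.

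5. **This is a condensed article on a pilot effectiveness study that openly admits the lack of blinding.** Rosters and station layouts belong in a fuller protocol or manual, and their absence is no fault. But the article does not leave assessor masking to another document: it states that blinding is impossible. Admitting a limitation does not show that it is unavoidable.

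**Conclusion.** The claim that blinding is impossible holds for participants and for those delivering the programme. It is unsupported for outcome assessors, at least for the medical students. Partial assessor masking is feasible and would reduce, not remove, expectation bias in manual blood pressure, waist circumference and PACER.

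The size of that bias cannot be derived from the documents. A reader might take 15–18% (1 mmHg) or 34–44% (2 mmHg) as the trial's error rate for aim 3. They are not. They describe a test of mean systolic pressure under assumed SD and bias. Aim 3 counts students with a desirable status, so a small shift matters only for children near a cut-off. The calculation also starts from a true 5% rate with independent children, which four non-randomised whole schools do not guarantee. The figures show only that a bias well below one SD could matter in a comparison of this size. Nothing in the documents shows that such a bias will occur.

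The change is worth making because it corrects a stated position at little cost, but its benefit is confined to part of one primary aim.

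**What to change.** - Restate the limitation: participants and those delivering the programme cannot be blinded; outcome assessors will not be told school allocation where feasible, and this masking will be incomplete, especially in May.
- Use the same measurement team at all four schools.
- Roster anyone who monitors the website or supports the mentors, including any such graduate students or program staff, away from the blood pressure, waist and PACER stations.
- In May, measure away from programme displays and record each assessor's guess of the group, so that the degree of unmasking can be reported.
- If any of this cannot be done for a station, say so and why.

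The cost is briefing and rostering of existing people, with no added staff. The drawbacks are some constraint on who can work which station, chiefly PACER, and masking that is only partial.
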